### Questionnaire data collection

5.5

### Dietary omega-3 PUFA intake

5.6

Dietary omega-3 PUFA intake will be estimated using a semi-quantitative food frequency questionnaire (FFQ), with participants recording food types, intake quantities, and portion sizes using food photograph models (30). Trained researchers will assess dietary omega-3 PUFA intake based on the Chinese Food Composition Table (31).

Participants will also complete detailed dietary records for three consecutive days (including two weekdays and one weekend day) using a 3-day, 24-hour dietary recall form. Food portions will be weighed using calibrated scales (precision 0.1 g). Participants will record the time, type, cooking method, and weight of all consumed foods, with daily records documented through photographs and submitted to research staff for daily review to ensure data accuracy and completeness.

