### Three intervention groups

3.2

Omega-3 PUFA-enriched eggs group: Participants will consume one omega-3 PUFA-enriched egg daily, five days per week (Tuesday through Saturday) for 12 weeks. Participants will consume eggs uniformly in the morning to ensure intervention standardization. Monday and Sunday are designated as egg-free days, during which no eggs or egg-derived products are permitted. Eggs will be provided by a centralized supplier along with product quality inspection reports. Nutritional analyses for eggs used in the intervention and control groups will be conducted by the research team.

The omega-3 PUFA-enriched eggs used in this study were tested for nutritional composition by the Chengdu Food Quality Supervision and Inspection Institute in accordance with national standard methods. According to the first method specified in GB 5009.168-2016 (National Food Safety Standard: Determination of Fatty Acids in Foods), the total omega-3 content (sum of α-linolenic acid and docosahexaenoic acid) was 0.446 g per 100 g of eggs, including 0.335 g of α-linolenic acid (ALA) and 0.111 g of docosahexaenoic acid (DHA). Based on the first method of GB 5009.82-2016 (National Food Safety Standard: Determination of Vitamin A, D and E in Foods), the vitamin A content was 201 μg per 100 g and the vitamin E content was 4.41 mg per 100 g. Based on an edible portion of approximately 50 g per egg, each omega-3 PUFA-enriched egg provides approximately 0.223 g of total omega-3 fatty acids. According to the Chinese Dietary Reference Intakes (2023 Edition), the adequate intake (AI) of ALA for adults is 1,600 mg/day for men and 1,100 mg/day for women. The recommended adequate intake of DHA+EPA for adults is 250 mg/day, including 200 mg/day of DHA. Therefore, one omega-3 PUFA-enriched egg per day provides approximately 167.5 mg of ALA, accounting for 15.2% of the AI for women and 10.5% for men, and approximately 55.5 mg of DHA, accounting for 27.8% of the recommended adult intake, which can serve as an important dietary source of omega-3 fatty acids.

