Regular eggs group: Participants will consume one regular egg daily, five days per week (Tuesday through Saturday) for 12 weeks. Participants will consume eggs uniformly in the morning to ensure intervention standardization. Eggs will be provided by a centralized supplier along with product quality inspection reports. Nutritional analyses for eggs used in the intervention and control groups will be conducted by the research team.

Blank control group: Participants will maintain their habitual dietary patterns throughout the 12-week study period.

In addition, during the subsequent intervention period, regular testing of omega-3 and other components in each group will be performed to verify and ensure that the intervention dose is clear and reproducible. This study will allow participants to consume other foods containing omega-3 fatty acids, provided that detailed records are maintained in dietary logs. Dietary intake will be assessed using the Food Frequency Questionnaire (FFQ) combined with 3-day 24-h dietary recalls. Participants will be required to provide particularly detailed documentation of omega-3-rich foods. During data analysis, these dietary records will be rigorously analyzed to evaluate their potential impact on the study outcomes.

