For monitoring and assessing intervention adherence, the following methods will be employed: (1) Subjective assessment methods: The 3-day 24-h dietary recall and Food Frequency Questionnaire (FFQ) will be used to record egg consumption timing, quantity, and accompanying foods, with cross-validation between the two methods. Trained interviewers will conduct telephone follow-ups weekly using open-ended questions such as: “What did you eat for your three meals yesterday? Did you consume an egg? At what time?” (2) Objective assessment methods: Fasting venous blood samples will be collected to measure biomarkers of omega-3 fatty acid intake, specifically the Omega-3 Index (the percentage of EPA and DHA in total fatty acids in red blood cell membranes). (3) Process monitoring: Empty egg packaging from the previous week will be collected, and remaining egg counts will be verified against self-reported consumption.

Through this three-tier adherence management system (supply guarantee, reminder supervision, and biological verification), we will maximize the assurance, supervision, and monitoring of stable egg consumption behavior among elderly participants during the 12-week intervention period, thereby enhancing the internal validity of the study.

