
Several other limitations should be acknowledged. First, complete participant blinding will not be achievable due to the absence of egg distribution in the blank control group, which may introduce expectation or behavioral bias. Second, dietary intake and compliance will be partly self-reported, potentially leading to recall or social desirability bias. Such bias will be minimized through strict quality control, double data entry, and validation using objective indicators. Third, the 12-week intervention period in this study will be sufficient to evaluate the acute effects of omega-3 PUFA-enriched eggs on blood lipids, gut microbiota, and metabolomic profiles; however, considering the ecological resilience of gut microbiota, longer intervention durations or post-intervention follow-up will be beneficial for assessing the sustainability of these changes. Future research will explore 6-month intervention designs with washout periods to verify the stability of gut microbiota alterations. Finally, variability in cooking methods and dietary substitution may influence individual exposure levels and metabolic outcomes. Although boiled eggs will be provided to participants living near community hospitals, cooking practices cannot be fully controlled in elderly individuals with limited mobility. Therefore, dietary surveys and follow-up records will be incorporated for covariate adjustment and sensitivity analyses, enhancing the robustness of result interpretation.

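### The three-day diet record in Section 5.6 can only fall on Thursday-Saturday or Sunday-Tuesday, so it over- or under-represents egg days against the Tuesday-Saturday egg week

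*Protocol article*

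**What the plan says.** Section 5.6 names the FFQ as the instrument for dietary omega-3 intake and then adds a second one: "Participants will also complete detailed dietary records for three consecutive days (including two weekdays and one weekend day"). Which days are meant is not said. Section 3.5 has a three-day record handed in at Week 0 before the eggs are given out, and the later visits repeat the Week 0 procedures.

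Section 3.2 sets the egg week. For the enriched-egg arm: "Participants will consume one omega-3 PUFA-enriched egg daily, five days per week (Tuesday through Saturday) for 12 weeks". For the regular-egg arm: "Participants will consume one regular egg daily, five days per week (Tuesday through Saturday) for 12 weeks". On the other two days: "Monday and Sunday are designated as egg-free days, during which no eggs or egg-derived products are permitted". Table 3 repeats the egg-free Sunday and Monday for both egg arms. The blank arm keeps its usual diet and has no such cycle.

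The record has stated uses. In Section 3.3 the three-day recall and the FFQ "will be used to record egg consumption timing, quantity, and accompanying foods, with cross-validation between the two methods". Section 3.2 combines the two instruments and has the diet records analysed for the influence of other omega-3 foods on outcomes. Table 3 sends diet-survey data on egg eating in the blank arm into covariate or sensitivity analyses. The Discussion, on cooking methods and dietary substitution, says that "dietary surveys and follow-up records will be incorporated for covariate adjustment and sensitivity analyses".

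**The concern.** A three-day record is meant to stand for the usual week. Here the week has a fixed five-plus-two pattern, and the rule for choosing record days does not follow it. Three things are at stake.

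- **Cross-check in Section 3.3.** A correct FFQ answer of five eggs a week and a correct three-day record, scaled up, will disagree in a fully adherent person. The check would then flag discrepancies that are not real.
- **On-trial diet as a covariate or comparison.** The egg-day cycle exists only in the egg arms. A simple mean of the record therefore carries an error in those arms that the blank arm does not have.
- **Diet on egg-free days.** Sunday and Monday exclude egg products as well as eggs, so other foods may change on those days. The Discussion itself names substitution as a limitation. A Thursday-Saturday record holds no egg-free day, and no later analysis can recover what was not recorded.

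**Working it through.** **Inputs**
- Record rule: three consecutive days, two weekdays and one weekend day (Section 5.6). Saturday and Sunday are taken as the weekend.
- Egg days: Tuesday to Saturday. Egg-free days: Sunday and Monday (Section 3.2, Table 3).
- Omega-3 content: "was 0.446 g per 100 g of eggs", with an edible portion of about 50 g per egg (Section 3.2).

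**The protocol's own figure.** 0.446 g/100 g × 50 g = 0.223 g per egg. This reproduces the statement that "each omega-3 PUFA-enriched egg provides approximately 0.223 g of total omega-3 fatty acids".

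**All seven runs of three consecutive days**

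| Run | Weekend days | Egg days | Meets Section 5.6 |
|---|---|---|---|
| Mon-Tue-Wed | 0 | 2 | no |
| Tue-Wed-Thu | 0 | 3 | no |
| Wed-Thu-Fri | 0 | 3 | no |
| Thu-Fri-Sat | 1 | 3 | **yes** |
| Fri-Sat-Sun | 2 | 2 | no |
| Sat-Sun-Mon | 2 | 1 | no |
| Sun-Mon-Tue | 1 | 1 | **yes** |

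**Size of the error in a participant on schedule, unweighted mean**
- Scheduled intake: 5/7 = 0.714 egg/day; 0.223 g × 5/7 = 0.159 g/day omega-3.
- Thursday-Saturday: 3/3 = 1.00 egg/day; 0.223 g/day; 1 ÷ (5/7) − 1 = +40%.
- Sunday-Tuesday: 1/3 = 0.333 egg/day; 0.223 ÷ 3 = 0.074 g/day; (1/3) ÷ (5/7) − 1 = −53%.

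Scaled to a week, the two records read 7 eggs and 7 × 1/3 = 2.3 eggs, against 5 scheduled.

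**Does ordinary weekday/weekend weighting repair it?** With weights 5 and 2:
- Thursday-Saturday: (5 × 1 + 2 × 1)/7 = 1.00.
- Sunday-Tuesday: (5 × 0.5 + 2 × 0)/7 = 0.357.

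It does not.

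**Does weighting by egg day and egg-free day repair it?** With weights 5/7 and 2/7:
- Sunday-Tuesday: 5/7 × 1 + 2/7 × 0 = 5/7, which is exact.
- Thursday-Saturday: there is no egg-free day to weight, so the calculation cannot be made.

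**Does mixing the windows repair it?** If 4/7 of records were Thursday-Saturday and 3/7 Sunday-Tuesday, the group mean would be 4/7 × 1 + 3/7 × 1/3 = 5/7. Each individual value would still be off, and the protocol specifies no such mix.

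**The proposed days.** With Sunday plus two weekdays from Tuesday-Friday, the mean of the egg days is 1 and the egg-free day is 0. So 5/7 × 1 + 2/7 × 0 = 5/7, which matches the schedule.

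**The case against.** A reader might infer that on-trial egg and omega-3 intake as a whole is always wrong, or that adherence is mismeasured. The documents do not support that.

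- Section 5.6 makes the FFQ the estimator of dietary omega-3 intake; the three-day record is additional.
- Egg intake is also captured by a daily diary with video (Section 3.5) and by packaging and leftover counts (Section 3.3). Table 3 defines compliance as actual over required consumption, in its diary-based adherence row. Exposure is measured by the Omega-3 Index (Section 3.3) and plasma fatty acids (Section 5.2).
- Both egg arms share one schedule, so the rule itself creates no systematic difference in recorded egg frequency in the pre-specified primary comparison (Section 5.3). Section 7 adjusts for baseline diet and compliance, not for the on-trial three-day mean, and the Week 0 record precedes egg distribution.
- The protocol nowhere says that an unweighted mean will be used, and weighting is commonly left to the analysis plan. A Sunday-Tuesday record can be reweighted exactly.
- Nor does it say that participants choose their window. Section 3.5 refers to prespecified time windows, without naming days.
- Section 3.3 lets a missed egg be moved within the week, so real records can also show two or no egg days.

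All of this stands, and it confines the problem to a supporting instrument. It does not remove it. The other sources do not supply weighed whole-diet intake, which is what the record adds. Reweighting works for only one of the two permitted windows, and the choice of recording days is a data-collection rule that analysis cannot undo.

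**Conclusion.** The concern holds in a limited form. The record rule permits only two windows, and neither represents the egg week. For a participant on schedule, an unweighted on-trial mean of the record is off by +40% or −53% for the study egg, and weekday/weekend weighting does not cure it. A Thursday-Saturday record also leaves egg-free-day diet unobserved.

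The consequences are a weaker FFQ cross-check and a less reliable on-trial diet variable for adjustment, sensitivity analysis or comparison with the blank arm. The FFQ estimate, diary-based compliance, the baseline diet covariate, the triglyceride primary outcome and the sample size are untouched.

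The percentages assume full adherence to the Tuesday-Saturday schedule, a Saturday-Sunday weekend and a simple three-day mean. They concern the study egg only. Omega-3 from other foods is affected only if it differs between egg days and egg-free days, on which the documents give no figure.

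**What to change.** In Section 5.6:

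1. Drop the requirement that the days be consecutive. Fix the same record days for all arms and all visits: Sunday, which is both egg-free and a weekend day, plus two weekdays from Tuesday-Friday. This keeps the two-weekday, one-weekend-day rule and leaves the egg schedule as it is.
2. Compute the weekly mean in every arm as 2/7 × the Sunday value + 5/7 × the mean of the other two days.
3. State that study-egg intake and adherence are taken from the daily diary and egg counts, and that the three-day record serves for the rest of the diet.

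The cost is a change of wording and a weighted mean. There are still three recording days, and Table 1 lists the trial as not yet recruiting. The drawbacks are one extra reminder for non-consecutive days, and a less precise estimate of egg-free-day diet because it rests on a single day.

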### Physical activity

5.7

Physical activity will be assessed using the validated international physical activity questionnaire short form (IPAQ-SF). The IPAQ-SF is a self- or interviewer-administered instrument measuring the frequency (days per week) and duration (minutes per day) of walking, moderate-intensity, and vigorous-intensity activities across daily life contexts, and includes a sitting-time item to obtain both continuous and categorical physical activity data (32, 33). Participants will be categorized into low-, moderate-, and high-intensity physical activity groups according to official IPAQ scoring guidelines. To ensure data quality, appropriate data cleaning and truncation procedures (e.g., addressing unusually high durations) will be performed following established IPAQ recommendations, with methods transparently reported in statistical analysis (34). Given the older adult population in this study, previous reliability and criterion-related validation of the Chinese version of IPAQ (IPAQ-C) among Chinese older adults, using pedometer steps as a reference, supports its suitability for this population (35). Wearable devices will not be used to monitor physical activity.

### Sleep quality and duration

5.8

The pittsburgh sleep quality index (PSQI) will be used to assess sleep quality and duration among participants. The PSQI comprises 19 self-rated items and 5 observer-rated items (36, 37). A total score will be derived from the 19 self-reported items across seven domains: subjective sleep quality, sleep latency, sleep duration, habitual sleep efficiency, sleep disturbances, use of sleep medications, and daytime dysfunction. Higher total scores will indicate poorer sleep quality.

### Mood state scale

5.9

The Chinese version of the profile of mood states—abbreviated form (POMS-A) will be used to assess participants' mood states over the past week (including the current day). This 40-item self-administered scale comprises seven dimensions: tension, depression, anger, vigor, fatigue, confusion, and self-esteem. Participants will rate 40 affective adjectives on a 5-point Likert scale (0–4). Dimension scores will be summed; except for the positive dimensions (vigor and self-esteem), higher scores will indicate more negative emotional experiences (38–40).

The total mood disturbance (TMD) index will also be calculated to reflect overall emotional distress using the formula: TMD = (Tension + Anger + Fatigue + Depression + Confusion) – (Vigor + Self-esteem) + 100, with higher TMD scores indicating greater negative mood disturbance (41). The Chinese version of the POMS-A has demonstrated good internal consistency and usability in diverse populations, including older adults (38, 42).

### Cognitive assessment

5.10

This study will use the Chinese version of the montreal cognitive assessment (MoCA) to screen and quantitatively evaluate the overall cognitive function of participants. The MoCA is a rapid, pencil-and-paper screening tool that can be completed in approximately 10 min, with a maximum score of 30 points. It assesses multiple cognitive domains, including visuospatial/executive functions, naming, attention and calculation, language, abstraction, delayed recall, and orientation; higher scores indicate better cognitive function. The original validation of the MoCA recommended a cutoff score of 26 for identifying mild cognitive impairment (MCI) (43). Given that MoCA cutoff thresholds vary across cultural and demographic contexts—particularly among elderly populations with significant educational disparities—a localized validation of the Beijing version of the MoCA has been conducted in a Chinese community study (44). Recent systematic reviews and meta-analyses have shown that there is no fixed optimal MoCA cutoff for the Chinese elderly population; instead, the cutoff should be determined based on the study's objectives and the demographic characteristics (e.g., age, education level) of the participants (45). Therefore, in this study, MoCA scores will be treated as continuous variables, and potential confounding factors such as years of education and age will be adjusted for to ensure the robustness of the analysis.

### Physical measurements

5.11

At each study visit, trained research personnel will perform standardized anthropometric and blood pressure measurements, with results recorded on physical examination forms. All measurement devices will be calibrated and subjected to quality control procedures prior to use.

Height and Weight: Height will be measured to the nearest 0.1 cm using a wall-mounted stadiometer, with participants standing erect, barefoot, and without headwear. Weight will be measured to the nearest 0.1 kg using a calibrated digital scale, with participants wearing light clothing and no shoes. Each measurement will be performed twice, and the mean value will be recorded. If the difference between two measurements exceeds the predefined threshold, the device will be recalibrated and the measurement repeated.

Waist Circumference: Waist circumference will be measured to the nearest 0.1 cm using a non-stretchable measuring tape at the horizontal midpoint between the lower margin of the costal arch and the iliac crest. The measurement will be performed twice, and the mean value will be recorded.

Blood Pressure: Blood pressure will be measured using a validated automated sphygmomanometer or standard mercury sphygmomanometer (range 0–300 mmHg, accuracy ±2 mmHg). Systolic and diastolic pressures will be determined by Korotkoff sounds. Three measurements will be taken on the left arm, with the cuff fully deflated and a 30-s rest interval between measurements. Participants will remain seated quietly, with no speaking or movement during measurement. The mean of the three readings will be used for analysis.

Body Composition: Body composition will be assessed using a bioelectrical impedance analyzer. Participants will stand barefoot on the foot electrodes and grasp the hand electrodes with both hands, with thumbs lightly contacting the sensors, while maintaining a stationary position for approximately 60 s. Body composition reports will be archived as source documents.

## Confidentiality and withdrawal

6

All participants' personal information will be kept strictly confidential throughout the study. Unique identification codes will be assigned to each participant to manage their data during and after the trial, and personal identifiers will be stored separately from study data to ensure data security. Paper-based study materials will be stored in locked cabinets, and electronic data will be stored on encrypted servers with restricted access to authorized personnel only. Participants may voluntarily withdraw from the trial at any time without any penalty. Any adverse events that occur during the trial will be managed by emergency physicians to ensure participant safety.

## Data entry and analysis

7

**Data entry:** Questionnaire data will be collected directly via electronic forms with built-in logic checks to ensure the accuracy and completeness of data entry, minimizing errors in data recording.

**Statistical analysis:** Statistical analyses will be performed using SPSS 24.0 and R 4.2.0 software. For baseline variables, continuous variables will be analyzed using one-way analysis of variance (ANOVA) or kruskal-wallis tests, while categorical variables will be analyzed using chi-square tests or Fisher's exact tests.

For longitudinal outcome measures, mixed-model repeated measures analysis of variance (MMRM) with an unstructured covariance matrix will be adopted as the primary analytical method. This model will include intervention group, time point, and group × time interaction as fixed effects, with subject-specific random intercepts. Pre-specified covariates (including age, sex, body mass index (BMI), baseline dietary intake, physical activity, baseline clinical parameters, and compliance) will be adjusted in the primary analysis based on their correlation with outcomes and clinical relevance.

Missing data will be handled using intention-to-treat (ITT) analysis with mixed models, which can accommodate unbalanced data under the missing at random (MAR) assumption. Sensitivity analyses will include complete case analysis and multiple imputation by chained equations (MICE) to verify the robustness of the results.

For multi-omics analyses (microbiome and metabolomics), Benjamini-hochberg false discovery rate (FDR) correction (*q* < 0.05) will be applied to control the expected proportion of false positives among the results. Microbiome data will undergo centered log-ratio (CLR) transformation to address compositional data constraints. Non-parametric methods [Friedman test, permutation-based multivariate analysis of variance (MANOVA)] will be used when the assumptions of normality or homogeneity of variance are violated. Principal coordinate analysis (PCoA) based on bray-curtis distances will be used to analyze microbiome composition, and principal component analysis (PCA) will be applied to metabolomics data. Associations between the microbiome and metabolome will be analyzed using sparse partial least squares (sPLS) or canonical correlation analysis (CCA), with FDR correction applied to ensure the reliability of the results.

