### Sample size calculation

2.3

This three-arm randomized controlled trial will adopt an allocation ratio of 1:1:1. The primary outcome will be the change in fasting serum triglyceride (TG) levels from baseline to the end of the intervention. The main effect to be tested will be the difference in TG level changes between the omega-3 PUFA-enriched eggs intervention group and the regular eggs group. Based on previous dietary intervention studies in populations with metabolic syndrome, the estimated standard deviation of fasting serum TG is approximately 58 mg/dL (baseline TG level: 140.9 ± 58.0 mg/dL) (19). Sample size estimation will be based on data from a prior randomized trial, which reported a 35 mg/dL difference in triglyceride (TG) levels between participants consuming omega-3 PUFA-enriched eggs (152.476 mg/dL) and those consuming regular eggs (187.333 mg/dL) (20). Accordingly, the minimal clinically meaningful difference (δ) will be set at 35 mg/dL. Assuming a two-sided significance level of 0.05 and 80% statistical power (1–β = 0.80), the required sample size will be computed using the standard formula for comparing means between independent groups:

$$\begin{array}{l} N=\frac{2{\left(Z_{1-\frac{\alpha }{2}}+Z_{1-\beta }\right)}^{2}}{\delta^{2}} \end{array}$$

Where Z_1−α/2_ = 1.96, Z_1−β_ = 0.84, σ = 58 mg/dL, and δ = 35 mg/dL. Consequently, to meet the statistical power requirements for the primary comparison, approximately 44 participants per group will be needed. Considering a potential dropout rate of approximately 25% in 12-week dietary intervention studies among elderly populations (21), the sample size will increase accordingly:

$$\begin{array}{l} n=\frac{44}{1-0.25}\approx 59 \end{array}$$

Therefore, the final target sample size will be set at 60 participants per group, yielding a total of 180 participants across the three arms.

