### Primary outcome

5.3

The primary outcome will be defined as the longitudinal trajectory of fasting triglycerides (TG) measured at Weeks 0, 4, 8, and 12. The primary statistical analysis will focus on the group × time interaction, indicating differences in TG trends over time among intervention groups. The pre-specified primary comparison will be between the omega-3 PUFA-enriched egg group and the standard egg group to evaluate intervention efficacy. Exploratory pairwise comparisons will also be conducted for other group combinations not specified in the primary hypothesis.

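### The primary mixed model pairs an unstructured covariance with a redundant random intercept, and its unconstrained week-0 response makes the treatment contrast a valid but inefficient change-score comparison

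*Protocol article*

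**What the plan says.** Protocol article, section 7 (Data entry and analysis): "mixed-model repeated measures analysis of variance (MMRM) with an unstructured covariance matrix will be adopted as the primary analytical method". The next sentence, about the same model, lists group, time point and their interaction "as fixed effects, with subject-specific random intercepts". The adjustment list includes baseline clinical measures as a class; baseline TG is not named.

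Section 5.3 (Primary outcome) defines the outcome as the "longitudinal trajectory of fasting triglycerides (TG) measured at Weeks 0, 4, 8, and 12" and tests it by the group × time interaction, with enriched versus regular eggs as the primary comparison. Week 0 is therefore one of the response visits. Nothing in the protocol sets the group means equal at week 0.

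Section 2.3 (Sample size calculation) instead describes the outcome as the change in TG from baseline to the end of the intervention. It sizes the trial with a between-subject SD of 58 mg/dL and a difference of 35 mg/dL, and gives no correlation between visits.

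**The concern.** There are two separate problems in the one stated primary model.

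First, an unstructured covariance leaves nothing for a random intercept to explain. Fitted literally, the model has a flat direction in its covariance parameters. If the software stops, the analyst must decide which component to give up. Dropping the intercept leaves the intended model. Dropping the unstructured matrix and keeping the intercept imposes equal variances and equal correlations, which can change the standard error and p-value of the primary test. The text should settle that choice before data exist.

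Second, when week 0 is a response and each group has its own free week-0 mean, the treatment contrast subtracts the observed baseline difference in full. Randomisation makes the true week-0 means equal, and a model that uses this gains precision at no cost in recruitment.

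**Working it through.** **Inputs**
- From section 2.3: "Assuming a two-sided significance level of 0.05 and 80% statistical power"; "the estimated standard deviation of fasting serum TG is approximately 58 mg/dL (baseline TG level: 140.9 ± 58.0 mg/dL"); "the minimal clinically meaningful difference (δ) will be set at 35 mg/dL"; 1:1:1 allocation; 25% dropout; 60 randomised per arm, so 60 × 0.75 = 45 evaluable.
- Assumed: correlation ρ between week-0 and week-12 TG of 0.3 to 0.8, and the same SD at each visit.

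**The plan's own figure.** 2(1.96 + 0.84)² × 58² / 35² = 43.06, so 44 per arm; 44/0.75 = 58.7, so 59, set at 60. The plan's numbers reproduce, although the printed formula omits σ². They do not depend on the points below.

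**Redundancy.** Four visits give 4 × 5/2 = 10 distinct variances and covariances. The intercept variance adds the same constant to all 10. The map from 11 parameters to 10 elements has rank 10. As a check on simulated data, intercept variances of 0, 500, 1000 and 1300, each with the matching residual matrix, gave the same log-likelihood (−1900.595). The split cannot be estimated, but the sum of the two parts can, and the treatment contrasts depend only on that sum.

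**Efficiency of the week-12 contrast.** Per-subject variance:
- free week-0 means (change score): 2σ²(1−ρ)
- equal week-0 means, or baseline as covariate: σ²(1−ρ²)
- ratio: 2/(1+ρ)

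The standard error is the square root of (per-subject variance × 2/45). Power is from the noncentral t distribution. The n per arm for 80% power uses the plan's normal formula.

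| ρ | Variance ratio | SD, change / adjusted | Power at 45 per arm, change / adjusted | n per arm, change / adjusted |
|---|---|---|---|---|
| 0.3 | 1.54 | 68.6 / 55.3 | 67% / 84% | 61 / 40 |
| 0.5 | 1.33 | 58.0 / 50.2 | 81% / 90% | 44 / 33 |
| 0.6 | 1.25 | 51.9 / 46.4 | 89% / 94% | 35 / 28 |
| 0.7 | 1.18 | 44.9 / 41.4 | 95% / 98% | 26 / 22 |
| 0.8 | 1.11 | 36.7 / 34.8 | 99% / over 99% | 18 / 16 |

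A generalised least squares check with known covariance at ρ = 0.6 gave standard errors of 10.94 (free) and 9.78 (constrained). Adding a subject-level covariate as a main effect left the free-means contrast unchanged in complete data, so covariate adjustment of that form does not recover the lost precision.

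**Which remedy fits the group × time test.** Take two arms of 45, ρ = 0.6 at all visits and known covariance. The scale is σ²(1−ρ) = 3364 × 0.4 = 1345.6. The noncentrality is λ = (45/2) × SS/1345.6, where SS is the sum of squares of the visit-specific effects about their mean.
- Constant effect of 35 at weeks 4, 8 and 12, with week 0 as response: effects 0, 35, 35, 35; SS = 918.75; λ = 15.4 on 3 df; power 92%.
- Same effect, interaction over weeks 4 to 12 only: SS = 0; λ = 0; rejection rate 5%.
- Effect rising linearly to 35: SS = 680.6, λ = 11.4, power 82% with week 0; SS = 272.2, λ = 4.5 on 2 df, power 46% without it.
- Constant effect, all four visits, equal week-0 means: SS is replaced by Σd² − 0.2143(Σd)² = 3675 − 2362.5 = 1312.5, with d the effects at weeks 4, 8 and 12; λ = 21.9 on 3 df; power 98%. The factor is ρ/(1+2ρ−3ρ²) × (1−ρ) = 0.24/1.12 = 0.2143.

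**The case against.** The best defence is that little here touches the estimate. The redundant term leaves the marginal model unchanged, and most statisticians would simply drop it. The change-score contrast is unbiased under randomisation, matches the outcome that section 2.3 describes, and beats ignoring baseline when ρ exceeds 0.5. At ρ of 0.5 or more the written analysis meets the 80% target. The power figures rest on an assumed ρ, concern a single week-12 contrast rather than the full interaction test, and ignore partial data from dropouts that a mixed model retains. All of that stands. It limits the size of the point but does not remove it: the model sentence still contains two terms that cannot both be estimated, and below ρ = 0.5 the planned contrast falls short of 80% power while the adjusted one does not over the range shown.

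Three stronger readings are tempting and are not supported. A reader might infer that the whole primary model is unidentifiable; only the split of the covariance is. A reader might infer that the baseline measurement is wasted; it is used, but inefficiently. A reader might also infer that baseline TG enters as both response and covariate. That would be a serious fault, because the likelihood would grow without limit as the coefficient approached 1 and the week-0 residual variance approached 0. But section 7 mentions baseline clinical measures only as a class and does not name TG, so this is a possibility to close off, not an error in the text.

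The degrees-of-freedom method and a fallback order of covariance structures are ordinary analysis-plan content, and their absence from the article is no fault.

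**Conclusion.** The point holds in limited form. Certain from the text: the random intercept duplicates part of the unstructured covariance, and week 0 is a response visit with unconstrained group means. Treatment contrasts remain estimable and unbiased, and nothing here shows type I error inflation. The loss is precision: the variance is 11% to 54% larger than necessary for ρ from 0.8 down to 0.3, or 3 to 17 percentage points of week-12 power for ρ from 0.7 to 0.3. These sizes assume the stated SD of 58 at every visit, 45 evaluable per arm and a true difference of 35 mg/dL; ρ is not given in the protocol.

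**What to change.** In section 7, delete the random-intercept clause and keep the unstructured within-subject covariance. Keep weeks 0, 4, 8 and 12 as the response, constrain the group means to be equal at week 0 (constrained longitudinal data analysis), and state that baseline TG is not also entered as a covariate. The group × time test in section 5.3 is retained and gains power. The cost is a change of analysis wording, with no effect on sample size, visits or measurements. Table 1 lists the trial as not yet recruiting.

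The alternative is to model weeks 4, 8 and 12 with baseline TG and baseline TG × visit as covariates. This costs more. The primary test in section 5.3 and the abstract must then change from the interaction to a named enriched-egg versus regular-egg contrast, for example at week 12 in line with section 2.3. Without that change, the interaction over post-baseline visits would miss an effect that is constant from week 4 on.
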